#### Primary outcome: couples-based voluntary counseling and testing for HIV

To assess whether our primary outcome of HIV testing has been accomplished, we provide CHCT for study participants. If participants report being tested at an alternate site we will request that they re-test at our facilities to confirm the primary outcome. The testing counselor (a female from the study community) acts separately from the intervention and assessment staff and has no other interactions with participants.

CHCT is conducted in fixed spots in the community using mobile caravans. The CHCT walk-in service is provided once a week in each fixed spot and two days a week are reserved for appointments. The couples make appointments by contacting the study staff by text message or telephone call. The walk-in service is also available to couples on the day of randomization (the first group session); couples are allowed to take up the service immediately after randomization irrespective of their study group allocation. This ensures equal exposure and access to testing for both groups, beginning at the time of randomization.

The Centers for Disease Control and Prevention (CDC) model of HIV counselling and testing to couples was adopted [61]. Same-day rapid testing is conducted with strict confidentiality measures, and includes the following provided by a trained CHCT counselor: pre-test counselling, testing, results interpretation, post-test counselling, and referrals to both members of a couple. Pre-test counselling session includes exploring the couple’s life stage and reason for seeking CHCT, HIV risk concerns are also discussed, and possible test results are discussed intensively. Immediately after testing, couples are provided with their results and the CDC procedures for providing concordant or discordant results are followed. Post-test counselling includes prevention, care, and support discussions, and information on community resources. All couples who have come for CHCT or for information about CHCT are given an information pack regarding resources for care and treatment facilities and other important services available in the community and surrounding areas.

#### Quality assurance/quality control

Prior to trial initiation, all staff received training in study protocol and procedures. Training was specific for each team, with some general training for all staff with regard to ethics, confidentiality, and screening for coercion for participation by partners. The intervention team received specific training in providing relationship skills to couples. Training in conducting CHCT was given to the testing counselor in line with CDC and South African testing guidelines. Extensive practice sessions were conducted and observation by the Project Director and site principal investigator (PI) ensured competency for all staff prior to initiation of trial activities.

Quality assurance (QA) is integral to all activities, and is divided into three components: recruitment, surveys, and CHCT and intervention. First, a directly observed model utilizing scoring sheets is used for all three components and employees are provided with feedback immediately after. This directly-observed QA is conducted by a field supervisor in the field routinely for a sample of all couples undergoing each activity. Second, a laboratory-based model is used for QA of CHCT. All HIV testing practitioners are required to perform proficiency panels in field conditions using rapid test kits with blinded sera quarterly. The compulsory proficiency score is 100%; in cases where a score is less than 100% retraining will be offered. An HSRC site senior nurse supervises the process of panel proficiency testing. Finally, the intervention QA is divided into two parts: 1) a directly observed system with scoring sheet; and 2) tape recordings of couples’ counselling sessions. Group session one and group session two QAs are sampled for 5% of total group sessions for all facilitators. The intervention supervisor directly observes facilitation during group sessions and provides scores and feedback to facilitators. Couple counselling sessions are digitally recorded, with participants’ consent. Counsellors listen to each other’s audio files and provide feedback to each other under the guidance of their supervisor. Any staff member that scores in a manner that indicates under-performance is provided additional training and re-evaluated.

#### Data management

For quantitative surveys, the data are collected in the field on mobile phones, and uploaded to a central database. This method has been used in other large-scale studies (over 13,000 participants in total) being conducted at the study site.

#### Data analysis

##### Primary outcome: CHCT

There are two primary outcomes for our trial: 1) participation in CHCT; and 2) sexual risk behavior. We hypothesize that:

1) The proportion of participants who participate in CHCT by 9-month follow-up will be higher in the intervention group than in the control group.

2) The time to participate in CHCT as a couple will be shorter in the intervention group relative to the control group.

Our initial analyses to address these hypotheses will follow an intention-to-treat (ITT) approach and will be unadjusted. To evaluate hypothesis 1, a chi-square test will be used to compare the proportion of couples that participate in CHCT in the intervention group with the proportion of couples in the control group who participate in CHCT. To evaluate hypothesis 2, we will construct Kaplan–Meier curves to display the two groups’ survival functions and use a log-rank test to compare the two groups’ survival times. Both groups are getting equal exposure and access to testing, beginning from the participation in the first group. Couples will be the unit of analysis for hypotheses 1 and 2. The analysis for hypothesis 1 does not account for when the testing actually occurred, but only examines differences between the intervention and control group at the time of final 9-month follow-up. The analysis for hypothesis 2 will allow us to conduct more nuanced comparisons as to the timing of testing, for example, subsequent to the baseline survey, first intervention group, or follow-up interviews. Thus, we will have our primary comparison of intervention versus comparison group HIV testing within the entire study period at the final follow-up as our primary outcome, and other analyses will further illuminate specific patterns of testing over the course of the study due to intervention participation or exposure. For example, it may be possible that the couples in the intervention condition may exhibit an average longer time to testing when compared to those in the control condition. We will be able to investigate any group differences in timing of testing via our proposed time-to-event analyses.

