#### Retention

Enrolling both partners increases the challenge of retention, and we have implemented several strategies. First, each participant is asked to provide a primary and secondary contact number during their initial screening visit. Second, during the baseline consent process, participants are asked if they are willing to be contacted by telephone for appointment reminders, as well as follow-ups for missed appointments. They are asked if they are willing to be visited at their primary residence if they miss a study visit, as well as any alternative residences. After participants have consented to participate in the study, a baseline tracking form is completed capturing the couple’s contact and location details, to the extent they have consented. Participants are asked to provide updated contact information at each follow-up visit. If a couple breaks up during the study, each partner is invited to complete a break-up assessment over the telephone. The assessment documents when the couple broke up, if they tested for HIV as an individual or couple before the break-up, and whether or not participation in the intervention contributed to the break-up. If the participant reports being tested between their last visit and the break-up, they are asked to complete a brief testing questionnaire about whether the intervention contributed to their decision to test. After completing the break-up assessment, the couple is discontinued from the study, and study staff will no longer contact them. All participants are provided with referrals to local counselling/support centers.

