#### Power analysis

With projected attrition of 20% due to break-ups and 10% due to other causes, we require 350 couples to be randomized in order to achieve the sample size target at 9 months of 245 couples at the final 9-month follow-up. As stated, our primary outcome is determined for only the final follow-up time point, and not for any other group differences at other intervention time points (for example, between first and second group session). The actual prevalence of couple HIV testing is unknown. Thus, for the proposed logistic regression analyses we computed the minimum detectable odds ratio assuming a low prevalence of couple HIV testing (10%) and a medium prevalence of couple HIV testing (30%). For these scenarios, the minimum detectable odds ratios were 2.85 and 2.18, respectively. This was calculated for 80% power. Given the resource-intensiveness of this study intervention, we believe a substantial odds ratio is needed to merit rollout of such an intervention on a public health scale. For time to couple HIV testing survival analyses, under the same assumptions, the minimum detectable hazard ratios are 2.70 and 1.77.

For our sexual behavior outcomes, the minimum detectable R^2^ values fall below 1% for this continuous variable, which is considered a ‘small’ effect size according to Cohen’s [62] criteria for the R^2^ statistic. We based our calculations on data which reported a base rate of 2.35 unprotected sex acts per 3 months (from the study by Genberg and colleagues [6]). We have 80% power to detect a reduction in the mean number of unprotected sex acts from a base rate of 2.35 to 2.04 or 2.12 depending upon the level of within-participant correlation of reported sex acts over time.

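### If couples are censored at break-up, the Kaplan-Meier curves for time to CHCT overstate the proportion tested; show cumulative incidence and label the log-rank test as cause-specific

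*Protocol article*

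**What the plan says.** Under Data analysis, Primary outcome: CHCT, hypothesis 2 is that "The time to participate in CHCT as a couple will be shorter in the intervention group relative to the control group". The method is Kaplan-Meier curves of the "survival functions and use a log-rank test to compare the two" groups, by intention to treat, unadjusted, with the couple as the unit.

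Under Retention, separated partners are invited to a telephone assessment. It takes the date of separation and asks about earlier testing: "if they tested for HIV as an individual or couple before the break-up". A further item concerns a possible effect of the trial itself, namely "whether or not participation in the intervention contributed to the break-up". Once this is done, "the couple is discontinued from the study, and study staff will no longer contact them".

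Under Power analysis, break-ups are counted as attrition together with other losses: "With projected attrition of 20% due to break-ups and 10% due to other causes". The number to randomize is set at 350, which leaves 245 at 9 months.

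No section says how a separated couple enters the time-to-event analysis, and none mentions competing events.

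**The concern.** Kaplan-Meier assumes that a censored couple would go on to test at the same rate as couples still observed. That is reasonable for a couple who cannot be traced. It does not describe a couple who have separated and been discontinued, since no later couples' test can be recorded for them. If they are censored at break-up, the curve describes uptake in a setting where nobody separates, not the share of enrolled couples tested by a given time.

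Independence between break-up and testing is also doubtful on the trial's own reasoning. The Background hypothesizes that couples with more intimacy, stronger commitment and clearer communication are more likely to test together, and couples low on these are plausibly the ones who separate. The intervention targets the same factors, and the break-up assessment asks whether the intervention contributed to the separation. Break-up may therefore depend both on arm and on propensity to test.

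At stake are the uptake read off the curves and the interpretation of the log-rank result. Hypothesis 2 sits under the primary outcome and has its own detectable hazard ratios (2.70 and 1.77), so readers will give it weight.

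**Working it through.** **The plan's own attrition figure.** 350 × (1 − 0.20 − 0.10) = 245, which matches. Break-ups are two thirds of the projected loss.

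**Inputs.** 20% break-up and testing prevalences of 10% and 30% come from Power analysis; 9 months of follow-up comes from Design. Assumptions: constant hazards over the 9 months, couples censored at break-up, and no modelling of the 10% lost for other causes.

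**Size of the overstatement.** Let c be the true proportion tested and b the proportion that separates before testing. Total hazard H = −ln(1 − c − b); testing hazard h = H × c/(c + b); the curve shows 1 − exp(−h).

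| c | b | H | h | Shown | Excess |
|---|---|---|---|---|---|
| 10% | 20% | 0.357 | 0.119 | 11.2% | 1.2 points |
| 20% | 20% | 0.511 | 0.255 | 22.5% | 2.5 points |
| 30% | 20% | 0.693 | 0.416 | 34.0% | 4.0 points |

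The relative excess is 12% to 13%.

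**Sensitivity to the timing of break-up and testing.** Now let 20% be the chance of break-up whether or not the couple has tested. The break-up hazard is k = −ln(0.80) = 0.223. Solve c = h/(h + k) × (1 − exp(−(h + k))) for h.
- Testing spread over 9 months: for c = 30%, h = 0.404 and the curve shows 33.2%; for c = 10%, h = 0.118 and it shows 11.1%.
- All testing in the first 3 months, so that only k/3 = 0.074 competes with it: for c = 30%, h = 0.372 and the curve shows 31.1%; for c = 10%, h = 0.109 and it shows 10.4%.

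**What the log-rank test compares.** Two cases, with break-up independent of testing within each arm and break-up splits that are illustrative.
- *Equal testing hazards.* With a chance of break-up of 10% versus 30%, simulation (175 couples per arm, 4,000 runs) gave two-sided rejection of 5.35% at 10% testing and 4.7% at 30%, against a nominal 5%. Unequal break-up alone does not distort the test.
- *Equal cumulative testing.* If 30% test in both arms and 20% versus 30% separate before testing, the testing hazards are 0.416 and 0.458 (from H = −ln 0.40 = 0.916, halved). Their ratio is 1.10, and the curves show 34.0% and 36.8%. With chances of break-up of 15% versus 25%, the ratio is 1.06 at 10% testing and 1.07 at 30%; with 10% versus 30% it is 1.13 and 1.15. Rejection in favour of the arm with more break-ups (nominal 2.5%) was 3.7% and 5.2% for the first split, and 6.3% and 10.5% for the second.

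The second case shows that equal uptake and equal testing hazards are different hypotheses. It does not show the log-rank test failing at its own.

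**The case against.** The strongest reply is that censoring at break-up is inferred. The article gives no censoring rule, such rules often sit in an analysis plan that is not shown, and the break-up assessment would also allow separated couples to be kept as untested to month 9, which fits intention to treat. This stands as a limit on the point. Still, discontinuation at break-up, break-ups pooled with other attrition, and an unqualified Kaplan-Meier analysis together lead to censoring unless another rule is written.

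A reader might infer that the arms can separate purely because break-up rates differ. The article does not support that. Where the curves diverge with equal uptake, the testing hazards themselves differ (0.416 versus 0.458), so couples still together really do test faster in one arm. For break-up to bias the log-rank test, it must be related to testing propensity. The Background makes that plausible, but nothing in the article gives its size.

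A reader might also infer that Gray's test should replace the log-rank test. That is a choice of estimand, not the correction of an error. With a testing hazard of 0.416 in both arms and 20% versus 30% separating before testing, cumulative incidence is 30.0% versus 27.8%, a difference that comes only from break-up. Hypothesis 2 asks about speed, and hypothesis 1 already compares the proportion tested.

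Finally, the effect is modest. With equal break-up and equal testing hazards in the two arms both curves shift alike, and the illustrative hazard ratios of 1.06 to 1.15 are far below the stated detectable 1.77 and 2.70. This stands too.

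**Conclusion.** The point holds in a limited form. Read naturally, the plan censors couples at break-up, and one minus Kaplan-Meier then overstates the cumulative proportion tested. At the projected 20% break-up, the excess is about 0.4 to 1.2 points when 10% truly test and 1.1 to 4.0 points when 30% do. The upper ends assume constant hazards and all break-ups before testing; the lower ends assume all testing falls in the first 3 months.

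The log-rank test is sound as a cause-specific comparison if break-up is independent of testing propensity. It is not a comparison of cumulative uptake, and dependence between break-up and testing could bias it in either direction by an amount the article does not allow one to estimate.

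The 9-month chi-square comparison, which the article designates as primary, is not affected. Nor can one say that the curves must disagree with the chi-square proportions, because the article does not define the denominator for separated couples.

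**What to change.** In the analysis of hypothesis 2:
- State how a separated couple enters the analysis.
- Display Aalen-Johansen cumulative incidence curves by arm, with break-up as a competing event dated from the break-up assessment.
- Keep the log-rank test, labelled as a cause-specific comparison among couples still together.
- Report the number and timing of break-ups by arm.
- Give Gray's test, or an analysis that keeps separated couples as untested to month 9, alongside the log-rank test.

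The cost is a few sentences and a little extra analysis, with no change to trial conduct. One limit remains: partners are only invited to the break-up assessment, so some dates may be missing. The plan should say how these are handled and report how many there are.

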#### Primary outcome: sexual behavior

In addition to CHCT, our intervention is designed to reduce sexual risk behavior for HIV. We hypothesize that:

1) During follow-up, intervention participants will report fewer acts of unprotected sexual intercourse with: a) primary sex partners; and b) outside sex partners, relative to participants in the control group.

2) During follow-up, intervention participants will report fewer concurrent outside (that is, secondary) sex partners relative to participants in the control group.

We will test longitudinal hypotheses using random effects models to examine changes in participant trajectories in sexual risk outcomes. These longitudinal analyses will treat the individual as the unit of analysis and will include an additional random intercept to account for within-couple response correlations. Initial analyses of sexual risk behavior will follow an ITT approach and include intervention group assignment, time of measurement, and an intervention group-by-time interaction term.

It is critical to optimize the accurate reporting of self-reported sexual risk behavior given its role as a primary outcome of our trial. To account for any possible bias, we have taken the following precautions: 1) we are using previously validated instruments; and 2) the assessment and intervention activities are conducted by different staff members. Thus, we do not expect any differential effects of social desirability reporting across arms of the study.

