**Methods/design:**

Heterosexual couples (N = 350 couples, 700 individuals) are being recruited to participate in a randomized trial of a couples-based intervention comprising two group sessions (one mixed gender, one single gender) and four couples’ counseling sessions. Couples must have been in a relationship together for at least 6 months. Quantitative assessments are conducted via mobile phones by gender-matched interviewers at baseline, 3, 6, and 9 months post-randomization. Intervention content is aimed to improve relationship dynamics, and includes communication skills and setting goals regarding CHCT.

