## Methods/design

### Objectives

Uthando Lwethu is a couples-based RCT to test the efficacy of providing relationship-based counseling (for example, targeting communication skills, improving commitment, and intimacy) to increase the rates of CHCT among a population of heterosexual couples in rural KwaZulu-Natal, South Africa. A second primary outcome is reduction of sexual risk behavior (that is, condom use with primary partner in the last 3 months). We hypothesize that by improving positive relationship dynamics among couples, their rates of CHCT will increase and the frequency of sexual risk will decrease.

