### Design

This is a RCT. We aim to recruit a baseline sample of 350 heterosexual couples, which will be evenly distributed between the intervention and control groups (see Figure 1 for flow diagram). The intervention is delivered to groups of approximately 20 couples per block. At the end of the first group session, facilitators randomize couples to one of two groups. Random allocation within blocks was used to ensure adequate balance for the subsequent blocks. Couples randomized to the intervention group are scheduled for the second group session, and couples in the control group are scheduled for their 3-month follow-up assessment. Couples randomized to the control group receive no additional intervention activities, and couples randomized to the intervention group receive one additional group session and four couples’ counseling sessions. Follow-up surveys are completed for both groups at 3, 6, and 9 months post-randomization.

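### Unprotected acts with the primary partner: the time-constant couple intercept does not cover same-wave correlation between partners, so the group-by-time standard error is too small

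*Protocol article*

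**What the plan says.** The abstract gives the sample: "Heterosexual couples (N = 350 couples, 700 individuals) are being recruited". Under Design, couples are the randomized units, "which will be evenly distributed between the intervention and control groups". Both partners are assessed "at baseline, 3, 6, and 9 months post-randomization". Objectives describes the second primary outcome as sexual risk behavior, "that is, condom use with primary partner in the last 3 months". Under Primary outcome: sexual behavior, the first hypothesis is that "intervention participants will report fewer acts of unprotected sexual intercourse with: a) primary sex partners; and b) outside sex partners", compared with control.

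The same section sets the model. It will use "random effects models to examine changes in participant trajectories in sexual risk outcomes", and then: "These longitudinal analyses will treat the individual as the unit of analysis and will include an additional random intercept to account for within-couple response correlations". The initial analyses are by intention to treat and "include intervention group assignment, time of measurement, and an intervention group-by-time interaction term".

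The word *additional* implies participant-level random effects as well, though their form is not given. The couple intercept is the only within-couple term named. The section does not say which coefficient or contrast decides the hypothesis.

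**The concern.** At each wave the two partners give two readings of what is largely one couple-level count. If a couple has more unprotected sex in one 3-month window than is usual for them, both reports rise together at that wave.

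The couple intercept captures that some couples are always higher than others. It does not capture this wave-specific shared movement. With only the terms named, the movement falls into a residual that is treated as independent between partners.

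This matters most for change over time. The baseline survey precedes randomization, so if baseline is in the model, the group main effect is essentially a pre-treatment difference and the group-by-time term carries the treatment effect. That is the contrast the couple intercept does not protect. The error is anti-conservative on a declared primary outcome: intervals are too narrow and false positives too frequent.

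**Working it through.** **The plan's own figures.** The article states no standard error, r or type I error for this test, so there is nothing to reproduce directly. Its Power analysis gives a detectable drop from 2.35 to 2.04 or 2.12 acts. This cannot be confirmed, because the SD, the within-participant correlation and alpha are not given. That text mentions correlation within participants over time and none between partners.

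**Inputs.** From the article: couples randomized 1:1; 2 partners; 4 waves (baseline, 3, 6 and 9 months); 350 × (1 − 0.30) = 245 couples at 9 months. Assumed: two-sided alpha of 5%, a linear model, balanced complete data, and the values of r.

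**Model.** For couple *i*, partner *j*, wave *t*, let Y = fixed part + c_i + p_ij + w_it + e_ijt. Here c is the couple intercept, p the participant intercept, w the shared couple-by-wave part (variance s_w², taken as independent across waves) and e the individual residual (variance s_e²). The plan names c and participant effects, but no w. Define r = s_w² / (s_w² + s_e²).

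**Time contrast.** Take weights a_t that sum to zero, with A = Σ a_t², and average over the two partners. Both c and p cancel.
- True variance per couple: A (s_w² + s_e²/2).
- Variance under the planned model, whose residual variance is s_w² + s_e² and independent between partners: A (s_w² + s_e²)/2.
- Ratio: (2 s_w² + s_e²) / (s_w² + s_e²) = 1 + r.

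So the correct SE is sqrt(1 + r) times the model's, and the true type I error is 2[1 − Φ(1.96 / sqrt(1 + r))].

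| r (assumed) | SE factor | model SE too small by | 1.96 / sqrt(1 + r) | true type I error |
|---|---|---|---|---|
| 0.1 | 1.05 | 5% | 1.87 | 6.2% |
| 0.3 | 1.14 | 12% | 1.72 | 8.6% |
| 0.5 | 1.22 | 18% | 1.60 | 11.0% |
| 0.8 | 1.34 | 25% | 1.46 | 14.4% |

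**Simulation under the null** (245 couples, 2 partners, 4 waves, 4000 runs per setting). With couple and participant intercepts, rejection was 4.4%, 9.0%, 10.8% and 14.3% at r = 0, 0.3, 0.5 and 0.8. A test on couple-level slopes held 4.6% to 5.1%. REML fits at r = 0.5 gave a mean SE of 0.0402 without a couple-by-time component and 0.0491 with one. The ratio is 1.22 = sqrt(1.5).

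**Participant random slopes.** A participant slope adds variance that is independent between partners. The ratio becomes 1 plus the shared fraction of the contrast variance, which still exceeds 1 whenever s_w² > 0. Simulated rejection was 8.5%, 10.3% and 13.6% at r = 0.3, 0.5 and 0.8. That series gave 6.6% at r = 0, so the argument rests on the algebra and the simulation only supports it.

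**Arm difference averaged over T follow-up waves.** The weights no longer sum to zero. The variance of a couple mean is s_c² + s_p²/2 + s_w²/T + s_e²/(2T), where s_c² and s_p² are the variances of c and p. The freely estimated couple variance absorbs the s_w²/T term. Simulated type I error was 4.8% to 5.5% at r = 0.3 to 0.8, and at r = 0.5 the model SE equalled the correct couple-level SE (0.1269 for both). A follow-up average minus baseline, by contrast, has weights that sum to zero and belongs with the affected contrasts.

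**The case against.** **The decisive contrast is not fixed.** The hypotheses are worded as levels during follow-up, and group-by-time is only a term the model includes. If the primary estimate is the arm difference averaged over follow-up, the planned couple intercept is enough. This stands, and it limits the point to time contrasts. Against it, the section speaks of changes in trajectories and names the interaction, so group-by-time is a plausible primary test.

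**The residual structure is inferred.** The article does not say that the couple intercept is the only allowance for dependence. A condensed article may leave residual covariance or robust variance to an analysis plan not shown here, and that plan could already supply the remedy. This also stands as a condition. But the article does commit to a specific within-couple term, and that term cannot do the work needed for change over time.

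**r is unknown and may be small.** Partners are interviewed separately by gender-matched interviewers, and no figure on their agreement is given. At r = 0.1 the error is 6.2%, which is modest. The size is therefore a range. The direction is firmer: two people counting the same acts should give r above zero unless their reports are unrelated over time.

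**A reader might infer that the couple intercept is the only random effect.** The text does not support this, since that intercept is additional to participant-level effects. Those effects do not remove the problem.

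**Conclusion.** The point holds for hypothesis 1a and for contrasts over time, including group-by-time. With the terms the article names, the model-based SE is too small by a factor of sqrt(1 + r), and a nominal 5% test has a true error of about 6.2% to 14.4% for r between 0.1 and 0.8. This rests on a linear model, balanced data, a shared part independent across waves, and no further covariance term or robust variance in the unseen plan. A count model should err in the same direction, but by a different amount.

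Three stronger readings are not supported:
- **All sexual-behavior results are affected.** Acts with outside partners (1b) and numbers of outside partners (hypothesis 2) are not shared reports. Couples' HIV testing is analysed with the couple as the unit.
- **The data are counted as nearly twice the information they hold.** The variance ratio is 1 + r, so this needs r near 1, and the documents give no r.
- **Every treatment contrast needs correcting, or the outcome distribution must change.** The averaged arm difference needs no correction on this ground, and the choice of distribution is a separate matter.

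**What to change.** For hypothesis 1a, state that the group-by-time test will be reported in one of two ways:
- with couple-clustered (sandwich) variance; or
- with a couple-by-wave random effect, or a same-wave residual covariance between partners, added to the planned couple and participant effects.

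If shared movement is expected to persist from wave to wave, the clustered variance is the safer choice, because it does not need the form of the dependence to be right.

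No new data are needed, and the change can be made before analysis, since recruitment was still open at the time of the article. The cost is somewhat wider intervals, by sqrt(1 + r) for this contrast: 14% at r = 0.3 and 22% at r = 0.5.
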